### Data analysis

Patient notes review: a pre-post intervention analysis through time series analyses. The appropriateness of observations, incidence of late signs of deterioration, in-hospital mortality and admissions to ICU will be used as the primary measures of patient management. Successful intervention will be identified by a statistically significant increase in applicable actions and a reduction in the proportion of late signs, in-hospital mortality and admissions to ICU.

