#### Clinical impact measures

The impact of the interventions will be assessed on the proportion of patients that progress from early to late signs of deterioration and the quality of nursing care (primary measures). As per our previous studies we will use validated data extraction tools to mine data from patient observation charts. Appropriate frequency of vital signs and evidence-based responses to deterioration will be proxies for the quality of nursing care. Secondary measures include in-hospital mortality and admissions to ICU, and cost of provision of face-to-face versus web based education. We will also investigate stakeholder views and attitudes through semi-structured interviews with three key stakeholder groups at each site.

Patient sample size: Pilot data from an earlier rural study indicated that early signs of deterioration were present in 28 % of patients while late signs were present in 10 %, and that the total sample size required to detect a 5 % reduction in late signs of deterioration with a level of significance of 5 % and a power of 0.8 is 434 patients (217 before and 217 after the intervention) at each site [29].

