### Data collection tools

#### Patient medical records review

Using patients’ demography, diagnoses and vital signs data, outcomes will be measured in relation to deterioration including ICU admissions and mortality rates, etc. Further, based on our sample size calculations and the guidance produced by Harrison et al. [38], McQuillan [39] and NICE [40] we aim to identify a change in patient management by measuring the applicability of physiological observations, actions in relation to deterioration, and early and late signs of deterioration to identify improvements in performance (Table 2). We have developed and tested a chart audit tool based on a rationale for item inclusion, definitions, and clinical expert ratings of relevance and clarity with a high Content Validity Index of 0.83 [41]. We will therefore extract data from patient records from 80 randomly selected cases from each month, three months before the simulation intervention, and from each month for three months after the intervention (total *n* = 480 at each site). A post-hoc sensitivity analysis will be conducted to assess the representative nature of the sample.

**Table 2 Tab2:** Early and late signs of patient deterioration [Adapted from Harrison et al. [38]

Parameter	Early signs	Late signs
Oxygen saturation	90–95 %	<90 %
Systolic blood pressure (mmHg)	80–100 or 181–240	<80 or >240
Heart rate	40–49 or 121–140	<40 or >140
Respiratory rate	5–9 or 31–40	<5 or >40
Glasgow coma scale	N/A	>2 point drop

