#### Knowledge and skill performance ratings

Participant demographics, questionnaire, and simulation performance will be described with the use of descriptive and inferential statistics. Measures of dispersion (means, medians, etc.) will be reported. There will be a range of nominal, ordinal and interval data (paired and unpaired) requiring tests such as Chi-square; McNemar; Mann Whitney U; and t-tests. Multivariate analysis (linear and logistic regression) will be used to identify predictors of performance. Simulation exercises will be rated by two researchers for inter-rater reliability. A significance level of *p* < .05 will be applied throughout.

Based upon a Generic Qualitative Design eight stakeholder focus groups will be completed (two at each site) in order to identify the perceived impact of the program(s) [52]. Core themes and outcomes will be identified using Miles and Huberman’s stages of data analysis [53]. Analysts will attribute nominal codes to narrative segments and group narrative segments to identify key themes. Emergent themes will be shared and collaboratively refined to achieve a consensus for reporting. The reporting of findings will by guided by the COREQ guidelines for reporting qualitative research.

The program is designed to run for 18 months with a seven month lead-in, to enable literature reviews, ethical approval, access arrangements and refinement of data collection tools. The training intervention will be compressed into a four month period and subsequent patient notes review, data analyses and report writing will take a further seven months.

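### The before-after chart contrast that decides success names no case-mix adjustment, although patients' demography and diagnoses are taken from the same records

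*Protocol article*

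**What the plan says.** Under Data analysis, the patient-level evaluation is "Patient notes review: a pre-post intervention analysis through time series analyses". The same paragraph gives the decision rule: "Successful intervention will be identified by a statistically significant increase in applicable actions and a reduction in the proportion of late signs", and it goes on to include in-hospital mortality and ICU admissions. No patient covariate, stratification or standardisation appears there.

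Under Patient medical records review, 80 randomly selected cases per month are audited for three months before and three months after training, 480 per site. That section also says "Using patients’ demography, diagnoses and vital signs data, outcomes will be measured in relation to deterioration including ICU admissions and mortality rates, etc". Its one safeguard for the patient sample is this: "A post-hoc sensitivity analysis will be conducted to assess the representative nature of the sample".

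Modelling is named in two other places, for other purposes. Under Knowledge and skill performance ratings, "Multivariate analysis (linear and logistic regression) will be used to identify predictors of performance" refers to the nurses. Under Economic analysis, an adjustment for ICU admissions and mortality applies to hospitalisation costs.

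Under Participants, two wards receive the web program and two the face-to-face program. None is left untrained.

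**The concern.** The charts before and after training belong to different people admitted in different months. With no untrained ward, a before-after change in late signs mixes the training effect with any change in who was admitted. A between-program comparison cannot separate them either: both programs train their wards, and the Discussion says the intention is not to compare the two versions directly. Hypothesis (i) therefore rests on the within-ward change.

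Some change in mix is plausible. Data collection runs from February to November 2016, and training takes four months. If those ten months divide into three before, four of training and three after, the two windows fall in different seasons. That layout is an inference; the article does not date the windows. Six monthly points per site cannot tell a shift in mix from an effect of training.

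The representativeness check does not answer this. It asks whether the sampled charts resemble the patients they were drawn from. A sample can be perfectly representative in both windows while the ward population itself has changed.

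At stake is a primary result that could move in either direction with no change in nursing care, although patient data that would remove part of the confounding are already drawn from the records.

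**Working it through.** **Inputs from the article.** Under Clinical impact measures, "late signs were present in 10" % of pilot patients, and the sample size is "the total sample size required to detect a 5 % reduction in late signs of deterioration", read here as 10 % to 5 %. Charts per period: 3 × 80 = 240 at one site, 480 for a two-site program, 960 for four sites. Significance level 5 %, taken as two-sided (the article does not state sidedness).

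**The article's own figure.** It states 434 patients per site in total for 80 % power. The usual two-proportion formula for 10 % against 5 %, two-sided, gives 435 per period (870 in total). The match with 434 supports the absolute reading of the target. That it is labelled a total is a separate matter, which adjustment would not cure. The article gives no case-mix figure to reproduce.

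**Assumptions (not in the article).** Two strata. Central case: 30 % of patients are high-risk with a late-sign rate of 20 %; the rest have 6 %.

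*Step 1: bias with no training effect.* Crude rate = share × high rate + (1 − share) × low rate.
- Before: 0.30 × 0.20 + 0.70 × 0.06 = 0.102, close to the pilot 10 %.
- After, high-risk share 20 %: 0.20 × 0.20 + 0.80 × 0.06 = 0.088.
- Difference 0.014, which is 1.4 / 5 = 28 % of the target.

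*Step 2: range.* Bias = change in share × (high rate − low rate).
- Smallest: 0.05 × (0.18 − 0.07) = 0.0055, about 0.6 points.
- Largest: 0.15 × (0.25 − 0.05) = 0.030, or 3.0 points.

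*Step 3: false-positive rate for late signs, central case.* SE = √(2p(1 − p)/n) with p = 0.095. Rejection rate = Φ(δ/SE − 1.96) + Φ(−δ/SE − 1.96), with δ = 0.014.

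| Charts per period | SE | δ/SE | Rejection rate |
|---|---|---|---|
| 240 (one site) | 0.0268 | 0.52 | 0.082 |
| 480 (two sites) | 0.0189 | 0.74 | 0.115 |
| 960 (four sites) | 0.0134 | 1.05 | 0.182 |

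More charts make this error larger, because the bias stays while the SE shrinks.

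*Step 4: power under an opposite shift, 480 per period.* Training is assumed to halve risk in each stratum.
- No shift: 10.2 % to 5.1 %; power 0.85.
- High-risk share rises to 40 %: (0.40 × 0.20 + 0.60 × 0.06) × 0.5 = 0.116 × 0.5 = 0.058. The observed drop is 10.2 − 5.8 = 4.4 points; power 0.71.

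*Step 5: a second set of assumptions.* High-risk share 40 %, overall rate 10 %, risk ratio 2, 3 or 4. A 10-point fall in the share lowers late signs by 0.7, 1.1 or 1.4 points (14 to 27 % of the target). The chance of a falsely significant benefit (one direction, 2.5 % without a shift) becomes 4.5, 6.1 or 7.4 % at 240 per period and 7.6, 13.0 or 17.6 % at 960. A 10-point rise with training halving risk lowers one-site power from 54.8 % to 48.0, 44.3 or 42.0 %.

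All rates use a two-proportion z-test and ignore clustering.

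**The case against.** The strongest reply is that this is a condensed article, and a covariate list is commonly left to the analysis plan. The article never calls the contrast crude; time series analysis neither requires nor excludes covariates; and "demography, diagnoses and vital signs data, outcomes will be measured in relation to deterioration" links these data, loosely, to the outcomes. That stands as far as wording goes: the article names no adjustment, which is not the same as ruling one out. It does not dispose of the point. The article goes beyond silence: it states the deciding contrast and its success rule, offers a safeguard aimed at a different problem, and assigns regression and adjustment to other outcomes. Followed as written in a non-randomised design, it leaves measured confounding in the primary result.

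Several stronger readings are tempting and are not supported:
- *That case mix could create the whole target effect.* In the central case, removing every high-risk patient leaves 6.0 %, a drop of only 4.2 points.
- *That an opposite shift cuts two-site power from 0.84 to about 0.53.* This subtracts the full 1.4 points from a fixed 5-point effect, which needs training to take the low-risk stratum from 6 % to 1 %. Proportional halving gives 0.85 to 0.71.
- *That the rates in the table are false-success rates.* The success rule also needs a significant increase in applicable actions and reductions in other outcomes. The 0.18 further requires pooling all four sites, whereas the sample size is set per site.
- *That age is known to be extracted, or that the representativeness check follows the result.* The article says demography and post-hoc, no more.

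It is also fair that, with no untrained ward, time-related confounding is the larger threat, and that adjusting for demographic variables and broad diagnosis removes only part of it.

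**Conclusion.** The point holds as a weakness in how the primary clinical contrast is specified: no case-mix adjustment is named, and the only stated check on the patient sample cannot correct a change in ward population. It should be fixed.

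The likely effect is moderate. Under the assumed strata and shifts, it is a bias of about 0.6-3.0 points against a 5-point target, enough to raise the false-positive rate for late signs above its nominal 5 % and to erode power, but not to produce the target effect alone. The direction is unknown. The sizes depend wholly on assumed stratum rates and shifts, since the article gives no case-mix data; the second set of assumptions gives biases of similar size.

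**What to change.** Pre-specify the late-signs analysis as a chart-level logistic regression of late signs (yes/no) on period, with ward as a fixed effect, the demographic variables extracted (such as age and sex, if recorded) and broad principal-diagnosis group. A broad group is preferable to a complexity level that deterioration during the stay could itself change. Report the adjusted (standardised) risk difference with its 95 % CI beside the crude difference. Say in the plan that this adjustment does not remove confounding by trend, season or unmeasured acuity.

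The representativeness check would be more useful as a pre-specified monthly comparison of sampled charts with all ward discharges on the same variables.

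The cost is a few sentences and a little analysis time. The regression uses data the article already draws from the records; the monthly comparison also needs the same variables for all ward discharges. At 10 % before and 5 % after, a two-site program expects 480 × 0.10 + 480 × 0.05 = 72 patients with late signs, enough for a small model of six or seven terms. The downside is slight model dependence, which the crude result alongside makes visible.

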### Aim and hypothesis

This research aims to measure the impact of two forms of simulation education on nurses’ ability to detect and manage patient deterioration, to assess patient outcomes and to compare the total costs between the two interventions. The research hypotheses to be tested are:(i).Both the face-to-face and web-based models of simulation education will improve the detection and management of patient deterioration and patient outcomes.(ii).The web-based program will have lower total costs in improving the detection and management of patient deterioration and patient outcomes.

The primary outcomes to be measured are the proportion of patients showing late clinical signs of deterioration, and the quality of nursing assessment. The secondary outcomes to be measured are the cost of provision of face-to-face versus web-based training, together with stakeholders’ views and attitudes regarding the forms of program delivery, and change to in-hospital mortality and the rate of admission to ICU (see Fig. 1).

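### In-hospital mortality and ICU admission are secondary in two sections but primary in the analysis section, where they enter a success rule that leaves open which falls must be significant and at what level

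*Protocol article*

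**What the plan says.** Three sections of the protocol article assign a status to the same outcomes.

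- **Aim and hypothesis:** "The primary outcomes to be measured are the proportion of patients showing late clinical signs of deterioration, and the quality of nursing assessment". The next sentence lists the secondary outcomes, among them "change to in-hospital mortality and the rate of admission to ICU".
- **Clinical impact measures:** late signs and quality of nursing care are again primary, and "Secondary measures include in-hospital mortality and admissions to ICU".
- **Data analysis:** appropriateness of observations and late signs are joined by the other two, so that "in-hospital mortality and admissions to ICU will be used as the primary measures of patient management". A successful intervention is then identified by "a statistically significant increase in applicable actions and a reduction in the proportion of late signs, in-hospital mortality and admissions to ICU".

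The sample-size statement in Clinical impact measures concerns late signs alone. It gives no rate or target effect for mortality or ICU admission. Hypothesis (i) claims improvement in detection and management and also in patient outcomes.

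**The concern.** Data analysis holds the only success criterion in the article, and two outcomes that are secondary elsewhere help to decide it. The trial was not sized for either. The wording also leaves two things open: whether the requirement of statistical significance, attached to the increase in actions, extends to the three reductions, and whether the rule is applied per site, per program or over all four sites.

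At stake is what the trial may conclude. A program that improves both named primary outcomes could fail the rule because a secondary outcome did not move. Whether it fails could also depend on a reading chosen after the data are seen.

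**Working it through.** **1. Inputs from the protocol article.** Late signs fall from 10% to 5% (Clinical impact measures; the 5% reduction is read as absolute), with alpha 5% and power 0.8. Chart extraction (Patient medical records review) is 80 cases a month for three months before and three after. That is 80 × 3 = 240 per period per site, 480 per program (two sites) and 960 over four sites.

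**2. Inputs assumed.** Mortality 4%, ICU admission 3%, power 0.90 for the increase in actions, independent outcomes, no clustering, no time-series structure.

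**3. The plan's own figure.** The article gives 217 per period per site. The pooled two-sided two-proportion formula gives 435 per period, and power at 217 is 0.51. So 217 does not reproduce. That is a separate matter; the figures below use the planned extraction.

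**4. All four significant.** Power = Φ[(d − 1.96·SE0)/SE1], with SE0 = √(2p̄(1−p̄)/n) and SE1 = √((p1(1−p1)+p2(1−p2))/n).

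Late signs, n = 480: SE0 = √(2×0.075×0.925/480) = 0.01700; SE1 = √((0.09+0.0475)/480) = 0.01693; Φ[(0.05−0.03332)/0.01693] = 0.838.

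| Charts per period | Late signs 10→5% | Mortality 4→2% | ICU 3→1.5% | Joint, × 0.90 |
|---|---|---|---|---|
| 240 (site) | 0.548 | 0.249 | 0.197 | 0.024 |
| 480 (program) | 0.838 | 0.443 | 0.347 | 0.116 |
| 960 (four sites) | 0.986 | 0.729 | 0.601 | 0.389 |

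With 25% relative falls in mortality (4→3%) and ICU admission (3→2.25%) and late signs still halved, the program-level figure is 0.90 × 0.838 × 0.132 × 0.109 = 0.011.

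Range: take the same baseline for mortality and ICU admission, from 2% to 5%, each halved. Joint power is then:

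- site: 0.90 × 0.0115 to 0.90 × 0.0499 = 0.01 to 0.04
- program: 0.90 × 0.0508 to 0.90 × 0.2366 = 0.05 to 0.21
- four sites: 0.90 × 0.1887 to 0.90 × 0.6674 = 0.17 to 0.60

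**5. Only the increase in actions significant; the other three need only fall.** For each outcome take the binomial probability that the later count is below the earlier one, n = 480.

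- All halved: 0.90 × 0.998 × 0.960 × 0.930 = 0.80.
- Late signs halved, mortality and ICU admission down by 25%: 0.90 × 0.998 × 0.775 × 0.735 = 0.51.
- Late signs halved, mortality and ICU admission unchanged: 0.90 × 0.998 × 0.467 × 0.462 = 0.19. Each unchanged rare outcome falls by chance slightly less than half the time.

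**6. Comparison.** If success rested on the two outcomes named in Aim and hypothesis, both significant, the chance per program is 0.90 × 0.838 = 0.75, whatever happens to mortality and ICU admission.

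**The case against.** **The wording may be lenient.** The success sentence attaches statistical significance to the increase, while the reduction has its own article and no such qualifier. A reader might infer from step 4 that the rule is nearly unattainable, or that a program which truly halves late signs will almost always be declared unsuccessful. The text does not support that. It needs the strict reading, rates the article does not give, and analysis by site or program. On the lenient reading, success is about 80% per program when all rates halve. With four sites pooled, even the strict reading gives 39%. Positive correlation between outcomes would raise the strict figures: with correlations of 0.3 to 0.5 between test statistics, the 12% becomes about 18% to 22%.

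**There is only one success rule.** Aim and hypothesis and Clinical impact measures state no success criterion. What conflicts is the outcome hierarchy, so the 75% shows what a rule built on the named primaries would give; it is not a second rule in the plan. This stands.

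**A reader might also infer that any one of the four results suffices,** with an inflated false-positive rate. The components are joined by and, so this reading has no basis in the text.

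**Primary may be meant within a component.** Economic analysis names its own primary outcome although cost is secondary overall. This softens the conflict but does not remove it: Clinical impact measures and Data analysis both speak of measures and give these two opposite labels.

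**Hypothesis (i) covers patient outcomes.** Removing mortality and ICU admission from the success rule would leave that hypothesis out of step unless it is also annotated. This is right, and the fix allows for it.

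**Conclusion.** The point holds in this form. The contradiction in outcome status is explicit, needs no assumption, and reaches the only success criterion. The criterion is ambiguous on significance and on level of analysis, and two of its four components have no sample-size basis.

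How much this matters depends on the reading. If all four must be significant, power per program is about 12% with every rate halved and about 1% with 25% falls in mortality and ICU admission; with halving it is about 2% at one site and 39% with four sites pooled. If direction is enough, it is about 80% with every rate halved, but about 19% for a program that improves actions and halves late signs without moving mortality or ICU admission, against about 75% on the two named primaries. All these figures rest on the assumed baselines, the assumed 90% for actions, independence and no clustering. They show that the choice of reading decides the result; they do not forecast it.

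This is not detail that a separate analysis plan could supply: any such plan would have to contradict one of the article's own statements. It should be settled before the chart data are analysed.

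**What to change.** Align Data analysis with the other two sections:

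- Keep only late signs and quality of nursing assessment (appropriate observations and actions) as primary there.
- Define success as a significant increase in appropriate observations and actions and a significant reduction in late signs, each at two-sided 5%. Both are required, so no alpha adjustment is needed.
- State the level at which the rule is judged: site, program or all sites.
- Report mortality and ICU admission as secondary, with 95% confidence intervals and no success criterion.
- Add to hypothesis (i) that its patient-outcomes part is assessed as secondary.

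The cost is about two sentences in Data analysis and a clause in the hypothesis. No extra data are needed. The trial gives up a formal success claim on mortality or ICU admission, for which it has no sample-size basis.

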#### Knowledge and skill performance ratings

Participant demographics, questionnaire, and simulation performance will be described with the use of descriptive and inferential statistics. Measures of dispersion (means, medians, etc.) will be reported. There will be a range of nominal, ordinal and interval data (paired and unpaired) requiring tests such as Chi-square; McNemar; Mann Whitney U; and t-tests. Multivariate analysis (linear and logistic regression) will be used to identify predictors of performance. Simulation exercises will be rated by two researchers for inter-rater reliability. A significance level of *p* < .05 will be applied throughout.

Based upon a Generic Qualitative Design eight stakeholder focus groups will be completed (two at each site) in order to identify the perceived impact of the program(s) [52]. Core themes and outcomes will be identified using Miles and Huberman’s stages of data analysis [53]. Analysts will attribute nominal codes to narrative segments and group narrative segments to identify key themes. Emergent themes will be shared and collaboratively refined to achieve a consensus for reporting. The reporting of findings will by guided by the COREQ guidelines for reporting qualitative research.

The program is designed to run for 18 months with a seven month lead-in, to enable literature reviews, ethical approval, access arrangements and refinement of data collection tools. The training intervention will be compressed into a four month period and subsequent patient notes review, data analyses and report writing will take a further seven months.

